## Abstract

**Background:**

Polycystic ovary syndrome (PCOS) is one of the most common endocrine disorders in women and is diagnosed using the Rotterdam criteria, including diagnosis of polycystic ovarian morphology (PCOM) by transvaginal ultrasound (TVUS). Due to high cost, availability, and the impact of the operator and ultrasound equipment on the reliability of the antral follicle count (AFC) by TVUS, an unmet need exists for a diagnostic test to determine PCOM without TVUS. A strong positive correlation between elevated anti-Müllerian hormone (AMH) levels and AFCs has been demonstrated in women with PCOS. In addition, recent updates to the international evidence-based PCOS guidelines state that serum AMH can be used as an alternative to TVUS-determined AFC, in the diagnosis of PCOM. The retrospective APHRODITE study derived and validated an AMH cutoff of 3.2 ng/mL for the Elecsys AMH Plus or Elecsys AMH assays (Roche) to diagnose PCOM in patients with PCOS.

**Objective:**

This study aims to further validate, in an independent prospective cohort, the AMH cutoff (3.2 ng/mL) for PCOM determination, which was previously derived and validated in the APHRODITE study.

**Methods:**

This large, prospective, multicenter, population-based, noninterventional study will evaluate the previously established AMH cutoff for the determination of PCOM during the diagnosis of PCOS using the Elecsys AMH Plus immunoassay in an independent population. Participants were women born between July 1985 and December 1987 in Northern Finland; the study partially links to the Northern Finland Birth Cohort 1986. We assessed the enrolled women, determined with the 2023 PCOS Guidelines, for current PCOS status and divided them by phenotype if positive. Each participant had 1 study visit to collect serum samples, record clinical data, and undergo a gynecological examination including TVUS. All data were collected by highly trained midwives or trained gynecologists. Sensitivity, specificity, and agreement measures were used to validate the previously determined cutoff in the whole population and in subpopulations based on phenotype and relevant demographic or clinical factors. The minimum target sample size was approximately 1800 women, including approximately 10% with PCOS.

**Results:**

At the time of manuscript submission, participant recruitment had concluded, and 1803 women were enrolled into the study. Data collection is complete and biostatistical analysis is planned for 2023.

**Conclusions:**

To limit variability, there were few TVUS operators and only 2 TVUS machines of the same type. Additionally, all women who were taking oral contraceptives were excluded from the primary analysis population. Selection bias was limited as this was a population-based study and participants were not seeking treatment for PCOS symptoms. Validating the AMH cutoff in a large, population-based study will provide further evidence on the utility of the Elecsys AMH Plus or Elecsys AMH assays in PCOM diagnosis as an alternative to TVUS. Measuring AMH for PCOM diagnosis could reduce delayed or missed diagnoses due to operator-dependent TVUS examinations.

**Trial Registration:**

ClinicalTrials.gov NCT05527353; http://tinyurl.com/2f3ffbdz

**International Registered Report Identifier (IRRID):**

DERR1-10.2196/48854

## Introduction

Polycystic ovary syndrome (PCOS) is one of the most common endocrine disorders affecting women and is characterized by symptoms of ovarian dysfunction and an excess of androgen, without other specific diagnoses [1-3]. PCOS is the primary cause of female anovulatory infertility and has metabolic, cardiovascular, and psychological implications [4-7]. The diagnosis of PCOS is based on the Rotterdam criteria [8,9], where 2 or more of the following conditions should be met: oligoanovulation or anovulation (OA), clinical or biochemical signs of hyperandrogenism (HA), a combination of both, and polycystic ovarian morphology (PCOM) based on transvaginal ultrasound [10] (TVUS; Figure 1).

**Figure 1 figure1:**
[figure not shown]
Diagnostic criteria and phenotypes of PCOS based on the Rotterdam criteria. HA: hyperandrogenism; OA: oligoanovulation or anovulation; PCOM: polycystic ovarian morphology; PCOS: polycystic ovary syndrome.

According to the updated guidelines [9], the diagnosis of PCOM is based on a TVUS with a finding of ≥20 follicles of 2-9 mm in size in at least 1 ovary or increased ovarian volume ≥10 mL, but determination of the antral follicle count (AFC) by TVUS depends on the operator and ultrasound equipment used [11-17]. Due to the expense of the equipment and the regularity of updates needed, in addition to the very high level of specialized training required by operators, TVUS is not available for many physicians seeing women with symptoms of PCOS (eg, general practitioners, gynecologists, and endocrinologists). Thus, there is significant underdiagnosis of PCOS [18] along with a substantial delay in receiving a diagnosis [19-22]; therefore, an unmet medical need exists for a diagnostic test to determine PCOM without the need for TVUS.

Anti-Müllerian hormone (AMH) is a regulator of follicle recruitment from the primordial follicle pool and inhibitor of follicular growth that is expressed by granulosa cells in the preantral and small antral follicles [23,24]. Serum AMH levels correlate well with the 2-9 mm antral follicles found in TVUS examination in the diagnosis of PCOM [25,26]. Elevated levels of AMH are observed in women with PCOS [27-30], and a strong correlation between elevated levels of AMH and increased AFCs has been demonstrated [12,14,26,29], supporting the use of AMH as a biomarker for PCOM.

In the recent, retrospective, case-control APHRODITE study, a cutoff of 3.2 ng/mL for the Elecsys AMH Plus or Elecsys AMH assays (Roche Diagnostics International Ltd) was derived and validated to identify PCOM as part of PCOS diagnosis in women aged 25-45 years [28]. Moreover, a recent study reported the usability of the Elecsys AMH assay to identify PCOS cases in large epidemiological data sets [31]. All previous findings support the use of AMH measurement using the Elecsys AMH Plus assay as a substitute for AFC in the determination of PCOM, thereby reducing the need for TVUS procedures [28,32].

Since APHRODITE was a retrospective, case-control study that validated the derived cutoff in a population with an increased risk of PCOS, it is of interest to further validate the derived cutoff in a prospective, independent, population-based cohort. By validating AMH levels in a large, population-based study using the Roche Elecsys AMH Plus assay, we aim to provide clinicians with the ability to identify PCOM as part of a PCOS diagnosis using a simple blood test, thereby making diagnosis of the disorder more accessible in a primary care setting. Although it is not anticipated that TVUS as a diagnostic method for PCOM will be discarded from PCOS guidelines, AMH testing could be adopted as an alternative method, particularly in primary care.

## Methods

### Study Design

The prospective, multicenter, population-based, noninterventional HARMONIA (Human Anti-Müllerian Hormone for Diagnosis of PCOS) study aims to validate the AMH cutoff determined and validated in the APHRODITE study for the determination of PCOM during the diagnosis of PCOS using the Elecsys AMH Plus immunoassay. Study enrollment was conducted between May 2020 and October 2022 at 2 sites in Finland: Oulu University Hospital, Department of Obstetrics and Gynecology, Oulu, and Helsinki University Hospital, Helsinki.

### Participants

The target population was women born in Northern Finland between July 1, 1985, and December 31, 1987; the study partially links to the Northern Finland Birth Cohort (NFBC) 1986 study population. The prevalence of PCOS in this population is expected to be approximately 10% when applying the diagnostic criteria for PCOS outlined in the 2018 international PCOS guideline [9,33]. The COVID-19 pandemic resulted in a lower enrollment rate than originally expected, and so the cohort was expanded to include a random cohort of women born in the same geographical area up to 18 months after those in the NFBC 1986, to ensure enrollment met the minimum target sample size of approximately 1800 individuals. As the study is population-based, all nonpregnant women from the target population were invited to participate in the study.

Participants were excluded if they were unwilling to undergo gynecological examination including TVUS, refused to have blood drawn, or did not consent to sharing their personal data with Roche Diagnostics International Ltd, who completed the AMH measurement and analysis. Additionally, women who were taking oral contraceptives at the time of study commencement will be excluded from the primary analysis population.

PCOS cases were defined as women fulfilling 2 or more Rotterdam criteria [8,9]. For each participant, the current PCOS status was assessed. PCOS positive cases were further divided into the following phenotypes: phenotype A (HA+, OA+, PCOM+), phenotype B (HA+, OA+, PCOM-), phenotype C (HA+, OA-, PCOM+), and phenotype D (HA-, OA+, PCOM+; Figure 1). PCOM in PCOS cases included the PCOS A, C, and D phenotypes. PCOS phenotype B cases by definition did not meet the criteria for PCOM based on TVUS (phenotype B accounted for approximately 3% of PCOS cases in the APHRODITE study) and were not included in the case group for the primary objective. Controls were defined as women with negative PCOM with an AFC <20, an ovarian volume <10 mL, and no other diagnostic features of PCOS according to the Rotterdam criteria.

Each participant had 1 study visit during which serum samples were collected through blood draw (taken at any stage of the menstrual cycle), clinical data (including questionnaire responses) were recorded, and a gynecological examination including TVUS (Ultrasound System HS60, Samsung Healthcare) was performed to determine PCOM status; all assessments were evaluated by a clinician (Table 1) [34]. All data were collected by highly trained midwives or gynecologists.

**Table 1 table1:** Baseline characteristics to be recorded by questionnaire and clinical assessment.

Baseline characteristic	Questionnaire	Clinical assessment
General information and medical history	Participant identification and date of consent Age at the study visit Race Education History of radiation or chemotherapy (yes or no) or treatment Long-term illnesses diagnosed by a doctor (self-reported) Bothersome hair loss experience Acne (former or current)	Confirmation of fasting for 12 hours before the clinic visit
Medication use	Medication use (current) Use and type of hormonal contraceptives (oral, patch, or intrauterine device; former or current)	N/A^a^
Intoxications	Smoking (current, former, or never; number of cigarettes) Alcohol (units per week)	N/A
Obstetric history	Menarche Cycle (regular, irregular, or absent) Shortest and longest menstrual cycle length (days) Last menstrual cycle Number of live births, fetus mortus, miscarriages, extrauterine pregnancy, and pregnancy terminations Fertility treatment Breastfeeding status (no, exclusively, or partially) Delivery within 6 months from the study visit	From the transvaginal ultrasound report: Endometrial thickness Visualization status of the ovaries Ovarian length, width, height, and volume Antral follicle count Dominant follicle presence Presence of corpus luteum and/or cysts >25 mm and/or other possible reason for increase of the ovarian volume
Anthropomorphic	N/A	Height Weight Waist circumference Hip circumference Systolic blood pressure or diastolic blood pressure Gynecological ultrasonography (polycystic ovarian morphology) Hirsutism (Ferriman-Gallwey-Score) Acne severity grading (1-5) per the Global Acne Severity Scale [34]. Images of the participant will be assessed by a dermatologist

^a^N/A: not applicable.

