### Data Analysis

At the time of publication submission, the trial was still underway, although data collection was complete. During the planned biostatistical analysis, baseline characteristics and biomarker data will be analyzed for all participants, and by PCOS phenotype and case or control groups. Additionally, the baseline characteristics will be compared between cases and controls using statistical tests, such as Mann-Whitney *U* tests or chi-square tests.

The primary objective of this study, conducted in the PCOM positive population, will be validating the AMH cutoff for PCOM determined in the APHRODITE study. Agreement measures will be calculated, and tables produced to estimate the performance (ie, sensitivity, specificity, and receiver operating characteristic curve) of the prespecified Elecsys AMH cutoff for the prediction of PCOM status. In addition, performance estimates (sensitivity, specificity, and agreement tables) of the Elecsys AMH Plus cutoff will be performed within subpopulations (phenotype and potentially relevant demographic or clinical factors).

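### The group definitions leave PCOM-negative women with HA or OA alone out of the specificity estimate, although in them the AMH result decides the diagnosis; other sections describe the analysis set differently

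*Protocol article*

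**What the plan says.** Protocol article, Participants. On the case side, "PCOM in PCOS cases included the PCOS A, C, and D phenotypes", and phenotype B women "were not included in the case group for the primary objective". On the control side, "Controls were defined as women with negative PCOM with an AFC <20, an ovarian volume <10 mL, and no other diagnostic features of PCOS".

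The purpose is stated more broadly. The Introduction explains that APHRODITE was a retrospective case-control study in women at increased risk of PCOS, so "it is of interest to further validate the derived cutoff in a prospective, independent, population-based cohort". Data Analysis sets out to estimate the performance "of the prespecified Elecsys AMH cutoff for the prediction of PCOM status".

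Three other places describe the population analysed:

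- Abstract, Methods: the aim is to "validate the previously determined cutoff in the whole population and in subpopulations based on phenotype".
- Data Analysis: "The primary objective of this study, conducted in the PCOM positive population".
- Sample Size and Power: the two denominators are PCOS positive and PCOS negative women. The exclusions mentioned are hormonal contraceptive use, phenotype B, and PCOS or PCOM status that cannot be determined.

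Strengths and Limitations says bias will be limited because the study is population-based. It does not mention the restriction on cases and controls.

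**The concern.** The cohort was sampled from a population, but the group definitions bring back part of a case-control contrast: PCOM with PCOS on one side, women with no PCOS feature on the other. If AMH is related to HA or OA beyond its link with follicle count, or if follicle count is itself related to those features, leaving out the mixed women makes the test look better than it is for PCOM status.

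The specificity side matters more. A false-positive AMH does harm where it changes the diagnosis, which is in a woman who already has one other criterion. The article promotes AMH as a replacement for ultrasound in primary care, where that error would occur. As the groups are defined, the headline specificity contains no such woman.

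**Working it through.** **1. The plan's own figures.** Sample Size and Power uses a one-sided 0.05 level, joint power of 80%, and limits of 65% (cases) and 70% (non-cases). Power is P(X ≥ c | n, p), where c is the smallest count whose one-sided 95% Clopper–Pearson lower limit is at or above the limit. Joint power is the product of the two.

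- 55 cases at true 82.5% (c = 42): 0.911. 164 non-cases at true 80% (c = 125): 0.9025. Product 0.822.
- 88 cases at true 79% (c = 65): 0.903. 262 non-cases at true 78% (c = 196): 0.905. Product 0.817.

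The stated sizes reproduce and are not in dispute.

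**2. Where each woman goes.** Three yes/no criteria give eight combinations. Under the Participants definitions:

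| HA | OA | PCOM by ultrasound | Group | Does PCOM decide the PCOS diagnosis? |
|---|---|---|---|---|
| – | – | – | control | no; at most one criterion |
| + | – | – | neither | **yes** |
| – | + | – | neither | **yes** |
| + | + | – | neither (B) | no; already two |
| – | – | + | neither | no; at most one |
| + | – | + | case (C) | **yes** |
| – | + | + | case (D) | **yes** |
| + | + | + | case (A) | no; already two |

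Four of the eight combinations are in neither group. The decisive PCOM-positive women (C, D) are cases. The decisive PCOM-negative women are not controls. This step needs no assumed figure.

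**3. The other descriptions.** The whole population (Abstract) would include all eight rows. A PCOM-positive population (Data Analysis) has no negatives, so specificity cannot be estimated in it. PCOS negative (Sample Size), read literally, takes in isolated HA and isolated OA, but also isolated PCOM, whose women are reference-positive for the stated target. None of the three matches Participants, and none says that the omitted women enter the primary estimates.

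**4. Size, on assumptions.** The document gives no counts and no AMH distribution for the omitted women.

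*Mixture for sensitivity.* A/C/D are taken as 9.7% of the cohort (10% PCOS less 3% phenotype B) with sensitivity 79%. Assume isolated PCOM is 5–20% of the cohort, with sensitivity 0–20 points lower.
- Most favourable: no difference, 79%.
- Middle (10%, 10 points lower): (9.7 × 0.79 + 10 × 0.69) / 19.7 = 73.9%.
- Least favourable (20%, 20 points lower): (9.7 × 0.79 + 20 × 0.59) / 29.7 = 65.5%.

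*Mixture for specificity.* Feature-free women are taken at 78%. With isolated PCOM at 10%, PCOM-negative women are 100 − 9.7 − 10 = 80.3% of the cohort. Assume isolated HA or OA is 10–30% of the cohort, with specificity 0–10 points lower. Phenotype B (0.3% of the cohort) is ignored.
- Most favourable: no difference, 78%.
- Middle (20%, 10 points lower): 0.78 − 0.10 × 20/80.3 = 75.5%.
- Least favourable (30%, 10 points lower): 0.78 − 0.10 × 30/80.3 = 74.3%.

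*Simulation.* Latent normal variables for follicle count, AMH and HA/OA. Assumptions: 20% PCOM, 25% with HA or OA, 25% AMH-positive, AMH–follicle correlation 0.6–0.8, follicle–feature correlation 0–0.3, and AMH–feature correlation at a given follicle count 0–0.2. HA and OA are one combined feature, so phenotype B is pooled with the one-feature women.
- Sensitivity is overstated by 0 to about 9 points (largest: 0.667 against 0.575).
- Specificity is overstated by 0 to about 3 points (largest: 0.859 against 0.832).
- Between 29% and 35% of women are omitted.
- Specificity in the omitted PCOM-negative women with a feature lies 0 to about 13 points below the headline value (largest: 0.859 − 0.728 = 0.131).
- If features are unrelated to both AMH and follicle count, there is no bias. With a negative AMH–feature correlation at a given follicle count (−0.1, AMH–follicle 0.7, follicle–feature 0), the sign reverses: sensitivity is 0.603 in the restricted groups against 0.647 in all women, and specificity 0.841 against 0.849.

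**The case against.** Several counter-arguments carry weight.

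- *The target can be read as PCOM within PCOS diagnosis.* The Study Design section puts it that way. On that reading A/C/D is a reasonable case group, since isolated PCOM can never become PCOS through AMH. This stands, and it makes the sensitivity part the weaker one. It does not help specificity, because on the same reading the PCOM-negative women who matter are those with one of HA or OA.
- *The groups are not two extremes of ovarian morphology.* Controls run up to the same follicle-count and volume thresholds at which PCOM begins, and nobody is selected on AMH. This stands. The selection is on HA and OA only, and is milder than case-control sampling.
- *The article may not intend the Participants definition to govern.* The Abstract and the Sample Size section can be read more broadly, and subpopulation analyses are planned. This stands in part: it shows a conflict. It does not remove the gap, because the one subpopulation named, phenotype, covers A to D only, and women with isolated HA, OA or PCOM have no phenotype.
- *A restricted contrast serves like-for-like comparison with APHRODITE.* True, and a reason to keep it as a secondary or co-primary analysis.

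A reader might go further and infer that both estimates will certainly be inflated, that the 65% and 70% limits are passed by construction, or that the study is underpowered. The documents support none of these. The first depends on associations they do not report. On the second, even pessimistic inputs (45% of PCOM-negative women with a feature, specificity 60% in them against 80% in the rest) give 0.55 × 0.80 + 0.45 × 0.60 = 71.0%, still above 70%. Sensitivity can fall below 65% only under similarly harsh inputs (isolated PCOM twice as common as cases, sensitivity 55% against 80%: (0.80 + 2 × 0.55) / 3 = 63.3%). On the third, the sample sizes reproduce, and the wider denominators would contain more women.

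**Conclusion.** The point holds in this form. By the Participants definitions, specificity is not estimated in PCOM-negative women with exactly one of HA or OA, the women in whom a false-positive AMH would create a PCOS diagnosis. That follows from the definitions and the two-of-three rule alone.

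Upward bias is likely rather than certain. The Introduction reports raised AMH in PCOS, which makes the direction plausible, but nothing in the document fixes the size. Under the simulation assumptions the effect on overall specificity is small (up to about 3 points) and on sensitivity for PCOM in general moderate (up to about 9). The gap between the headline specificity and that in the omitted women could be larger (up to about 13).

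Separately, the four descriptions of the analysis set do not agree and must be reconciled.

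**What to change.** Before the biostatistical analysis starts, state one analysis set and use it in all sections:

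1. Primary (or co-primary) contrast by ultrasound PCOM status in all evaluable women not excluded for contraceptive use. The sensitivity denominator is all PCOM-positive women. The specificity denominator is all PCOM-negative women, including isolated HA, isolated OA and phenotype B.
2. Keep A/C/D versus feature-free women as the comparison with APHRODITE.
3. Report sensitivity and specificity separately in women with exactly one of HA or OA.
4. Align the Abstract, Data Analysis and Sample Size wording with this set. In particular, replace the statement that the primary objective is conducted among PCOM-positive women.
5. If the restricted contrast stays primary, qualify the limited-bias statement in Strengths and Limitations.

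The cost is wording and some extra tables. Ultrasound, AMH, HA and OA data have been collected, and numbers are not a constraint: about 90% of 1800, or 1620 women, are expected to be PCOS negative before exclusions, against a stated need of 164–262. The downside is that the headline estimates may be less favourable.

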### Sample Processing

A total volume of approximately 5 mL of serum was collected using VACUETTE Tube 9 mL CAT serum clot activator tubes (Greiner Bio One) and stored at –80 °C. Aliquots were sent to the Nordlab in Oulu for measurement of testosterone by liquid chromatography-mass spectrometry (Sciex Qtrap 5500, Ab Sciex). Additional measurements were performed on-site at Oulu (testosterone, sex hormone-binding globulin, follicle-stimulating hormone, luteinizing hormone, thyroid-stimulating hormone, and prolactin) on the COBAS e 411 analyzer (Roche Diagnostics International Ltd), which was used to assess some of the PCOS criteria. Additional aliquots were shipped to Roche Diagnostics GmbH, Penzberg, Germany, for determination of AMH biomarker levels (Textbox 1). AMH levels were measured using the Elecsys AMH Plus assay on the COBAS pro e 801 analyzer (Roche Diagnostics International Ltd). The measuring range of the Elecsys AMH Plus assay is 0.01-23 ng/mL and the coefficient of variance for repeatability is less than 3% [35]. Participants with AMH levels more than 3.2 ng/mL (the cutoff determined and validated in the APHRODITE study [28]) were classified as AMH PCOM positive, and those with results ≤3.2 ng/mL were classified as AMH PCOM negative.

Laboratory parameters to be measured from blood samples.
